## Abstract

Parkinson's disease (PD), an intractable condition impairing motor and cognitive function, is imperfectly treated by drugs and surgery. Two priority issues for many people with PD are OFF-time and cognitive impairment. Even under best medical management, three-fourths of people with PD experience “OFF-time” related to medication-related motor fluctuations, which severely impacts both quality of life and cognition. Cognitive deficits are found even in newly diagnosed people with PD and are often intractable. Our data suggest that partnered dance aerobic exercise (PDAE) reduces OFF-time on the Movement Disorders Society Unified Parkinson Disease Rating Scale-IV (MDS-UPDRS-IV) and ameliorates other disease features, which motivate the PAIRED trial. PDAE provides AE during an improvisational, cognitively engaging rehabilitative physical activity. Although exercise benefits motor and cognitive symptoms and may be neuroprotective for PD, studies using robust biomarkers of neuroprotection in humans are rare. We propose to perform a randomized, controlled trial in individuals with diagnosed mild–moderate PD to compare the efficacy of PDAE vs. walking aerobic exercise (WALK) for OFF-time, cognition, and neuroprotection. We will assess neuroprotection with neuromelanin-sensitive MRI (NM-MRI) and iron-sensitive (R2^*^) MRI sequences to quantify neuromelanin loss and iron accumulation in substantia nigra pars compacta (SNc). We will use these biomarkers, neuromelanin loss, and iron accumulation, as tools to chart the course of neurodegeneration in patients with PD who have undergone long-term (16 months) intervention. We will randomly assign 102 individuals with mild–moderate PD to 16 months of PDAE or WALK. The 16-month intervention period will consist of Training (3 months of biweekly sessions) and Maintenance (13 months of weekly sessions) phases. We will assess participants at baseline, 3 months (immediately post-Training), and 16 months (immediately post-Maintenance) for OFF-time and behaviorally and physiologically measured cognition. We will acquire NM-MRI and R2^*^ imaging data at baseline and 16 months to assess neuroprotection. We will (1) examine effects of Training and Maintenance phases of PDAE vs. WALK on OFF-time, (2) compare PDAE vs. WALK at 3 and 16 months on behavioral and functional MRI (fMRI) measures of spatial cognition, and (3) compare PDAE vs. WALK for effects on rates of neurodegeneration.

## Introduction

Parkinson's disease (PD) impairs motor and non-motor functions and affects up to 2% of those aged 65 or more years. Annual costs associated with PD, including Medicare and Social Security, are around $25 billion annually in the United States (1). PD is almost ubiquitously treated with levodopa, a drug with side effects including motor fluctuations and dyskinesia, resulting in reduced sleep quality, difficulty with activities of daily living (ADLs), anxiety about drug effect, being immobilized and experiencing pain, and compromising quality of life (QOL) (2). Cognition plays a crucial role in motor function and functional ADLs, but one or more cognitive domains are impaired in up to 80% of patients beyond 5 years with PD (3). Although research supports several exercise principles that address motor issues, relationships between exercise principles and cognitive benefits in PD are less clear. Unfortunately, PD drugs and surgery imperfectly address motor and non-motor function for most people with PD, with decreasing efficacy of medications over time as this neurodegenerative disease progresses (2, 4).

Approximately 75% of people with PD experience “OFF-time” when medications do not work properly, and medication-related motor fluctuations (MRMF) result. MRMF adversely impact QOL. OFF-time is measured by part IV of the Movement Disorders Society Unified Parkinson's Disease Rating Scale (MDS-UPDRS) (2). Annually, 10% of patients develop MRMF and response failures when no symptomatic benefit occurs after taking levodopa (5). Long-term treatment results in MRMF in most patients (6). Within 4–6 years of levodopa treatment, MRMF develop in about 40% of PD patients, and after >10 years, nearly 90% of patients develop dyskinesias (7). Reducing dopaminergic therapy can not only improve fluctuations but may also increase PD symptoms (8, 9) or delay the “on” state. A total response failure accounted for more than 60% of daily OFF-time periods among 327 patients with advanced PD (10). Evidence suggests that exercise therapies play an ancillary role in drug efficacy, yet relationships between exercise modalities and OFF-time in PD have not been explicitly studied. Abundant evidence supports exercise benefits for people with PD, yet almost no research has targeted those who experience OFF-time.

People with PD report wanting reduced MRMF/OFF-time and 24-h symptom relief (11). Painful OFF-time and cognitive impairment become more common as PD neurodegeneration progresses (12). Using Level II criteria from Movement Disorders Society (MDS) task force on cognitive impairment, half of PD patients have cognitive impairment within 3 years of diagnosis (13). In individuals with PD for 5 years, nearly 80% have comorbid cognitive impairment (3). Levodopa only partially treats cognitive impairment (14). PD-related deficits in spatial attention, spatial location, and perception of optic flow (15) cause orientation disability and impair mobility (16). Spatial cognition is supported by brain structures vulnerable to normal cerebral aging (16) and PD neurodegenerative processes (15). Impaired attention and executive function also result in impaired mobility, dual tasking problems, postural-gait disturbances, and falls (17, 18). MRMF are significant predictors of pain: OFF-time episodes promote reduced pain thresholds (19) and worsening pain (19).

Exercise is increasingly touted as being helpful for motor and cognitive symptom relief (20) and may be neuroprotective (21). Our hypothesis, based on preliminary data, is that exercise reduces PD patient OFF-time. Exercise can improve dopamine efficiency: animals that exercised possessed less of the dopamine transporter; dopamine stayed in their synapses longer, and cells receiving the dopamine signal had more binding sites on the D2 receptor for dopamine and could receive a stronger signal (22). In a cohort of naive patients within 1 year of diagnosis and not on any medications, positron emission tomography (PET) showed that exercise increased expression of D2 receptors (23). Thus, exercise may impact the patient experience of drug efficacy by reducing patient OFF-time.

Previous small studies suggested that exercise had a null or variable impact on levodopa plasma absorption rates. Mouradian et al. (24) found no effect of one bout of acute treadmill training on the plasma levels of levodopa or antiparkinsonian effects in a study of four men optimally treated with levodopa (24). In 10 patients, Carter et al. (25) demonstrated that stationary cycling resulted in a patient-dependent increase or decrease in levodopa absorption (25). However, exercise may increase clinical efficacy of levodopa via other mechanisms. Reuter et al. (26) noted a trend toward better levodopa absorption and decreased dyskinesias under exercise conditions compared to rest in 12 patients (26). In a study of 12 male patients, levodopa plasma behavior did not differ between rest and exercise days, but motor response was better 120 and 150 min after levodopa intake on exercise days (27). However, these early studies were conducted in only patients without OFF-time. Therefore, the findings do not generalize to the impact of chronic exercise on OFF-time for patients who regularly experience this debilitating problem. This project will evaluate whether exercise reduces OFF-time in PD patients who regularly suffer MRMF.

Short, high-volume to long-term programs have ameliorated MRMF (28). In a 12-week study, effects of general strength/fitness exercise and levodopa were complementary, improving muscle force, UPDRS scores, and mobility (29). Frazzitta et al. (9) noted that scores on UPDRS section IV, which assays OFF-time and MRMF, improved after 4 weeks of intensive physiotherapy. Moreover, 6-month and 1-year follow-up scores on the UPDRS-III (clinical motor examination) were better than the admission scores although the therapy had been discontinued several months prior (9). It is plausible, then, that if such an effect was examined after 4 weeks of therapy, the effects would have been even stronger had the training continued in a less intense maintenance program.

Exercise also benefits cognition in PD. Uc et al. (30) demonstrated improved executive function in 43 PD patients (30). Duchesne et al. (31) showed improved inhibition and motor skill learning following AE in early PD (31). David et al. (32) reported that resistance training improved attention and working memory in 38 mild-to-moderately affected PD participants (32). Studies now examine physical and cognitive training delivered simultaneously or in close series to determine best treatments for cognitive impairment (33). Consistent with animal literature, dual cognitive/physical challenge may be most effective in inducing beneficial, durable effects on the brain's structure and function (34). This project will also evaluate the effects of dual cognitive/physical challenge and its effects on neural activity.

Evidence of improved motor and cognitive behavioral function with correlating neural-level changes and reduced OFF-time suggests that exercise may be neuroprotective in humans with PD **[**21, 35]. AE improves function and structure of the central nervous system (CNS) in older adults (35). AE is also associated with improved hippocampal function in older adults (36) and spared age-related deterioration of white matter tracts (37). Exercise in humans and rats increases brain-derived neurotrophic factor, insulin-like growth factors, nerve growth factor, and vascular endothelial growth factor (35). Only animal studies have provided evidence for exercise-induced neuroplasticity of corticostriatal circuits affected in PD. Exercise has been implicated in modulating dopamine neurotransmission, altering synaptogenesis, and increasing cerebral blood flow (22). In a PD rat model, AE increased activation in ventral striatum and pallidum, while it improved motor deficits (38). With physiological biomarkers, we aim to show that exercise slows neurodegeneration in humans with PD. Novel imaging tools and sequences are available and allow us to elucidate this relationship if it exists.

We aim to show that exercise slows neurodegeneration in humans with PD. Clinicians currently primarily monitor disease progression using the MDS-UPDRS assessment, a non-reliable measure of neurodegeneration in substantia nigra (SN) and other areas damaged by PD. The physiological magnetic resonance imaging (MRI) measurement of neuromelanin (NM) loss and iron accumulation can more accurately reflect disease progression over time. At PD diagnosis, 50% of the melanized dopamine neurons (NM) in the SN pars compacta (SNc) have died (39). The SNc and SN pars reticulata (SNr) are predominantly NM and iron containing, respectively (40).

NM loss is accompanied by iron accumulation in astrocytes, microglia, and neurons. Neurodegenerative changes in NM and iron in the SNc can be quantified *in vivo* with NM-MRI (41). NM-MRI also detects progressive loss of NM as PD advances (42). Our published studies support the use of these measures. Using an automated, reproducible segmentation approach, our methods can detect significant PD-associated NM loss, iron accumulation, and microstructural damage in SNc (43–45). The NM-MRI approach proposed in this study achieves high scan–rescan reproducibility (ICC = 0.96) (45), generates more contrast and deposits less energy than other approaches (41), and has improved signal-to-noise ratio (SNR) in SNc compared to other approaches (41, 46). The NM-MRI approach has detected PD effects on SNc volume in two separate cohorts using two different MRI scanner models. With an NM-MRI contrast-based method to select the SNc region of interest (ROI), we have previously used the effective transverse relaxation rate R2^*^ to measure iron in SNc (47) and demonstrated that iron was significantly increased in SNc in PD (45). NM- and iron-sensitive MRI contrast regions in SN are largely non-overlapping in controls (48). The image processing method to select SNc ROI was based on NM-MRI contrast, which colocalizes with SNc-pigmented dopamine neurons (49). In this trial, we will use these imaging biomarkers to chart neurodegeneration in PD patients undergoing a previously tested intervention, with demonstrated clinical efficacy. We will evaluate a unique form of exercise in the PAIRED trial, which will be the first to examine the neuroprotective impact of partnered dance.

Figure 1 depicts a conceptual framework for multidimensional benefits of partnered dance aerobic exercise (PDAE). A meta-analysis of randomized, controlled partnered dance trials in PD demonstrated improved symptom severity and balance (50). PDAE has been shown to improve motor function measured by motor symptoms, balance, preferred, backward and fast gait, mobility, endurance, and QOL (51–56). PDAE shares qualities of effective rehabilitation programs for people with PD, including repetition, intensity, task progression skill building, dynamic balance, and continual adjustments to the environment. To facilitate motor learning and make PDAE more accessible, the instructor deconstructs complex movements into simpler elements. PDAE movements are synchronized with musical rhythms and a partner, both of which are external cues that facilitate movement (57). PDAE is a ballroom dance and thus an AE that expends at least three metabolic equivalents (METs) (58). This amount is similar to usual walking in older adults (59), a low–moderate AE. PDAE requires cognitive engagement on multiple levels across multiple domains and has improved visuospatial cognition (56). After PDAE, our pilot data showed that patients reporting OFF-time at baseline reported reduced MRMF.

**Figure 1 F1:**
[figure not shown]
Hypothesized beneficial outcomes of Partnered Dance Aerobic Exercise.

We offer two premises for our expected outcomes of our trial. Our premise for expected reductions in OFF-time post-Training and post-Maintenance phases of 16 months of PDAE is as follows: In our recently completed trial, we found that PDAE potentially reduces OFF-time in veterans with PD who reported MRMF. We randomly assigned 36 individuals with PD who reported experiencing OFF-time (11 female; age, 67.6 ± 7 years; UPDRS-III = 35.9 ± 11; PD duration = 7 ± 5 years) to 30 h PDAE or contact control (Education) over 3 months. PDAE participants improved more on the MDS-UPDRS-IV (which measures MRMF and OFF-time) (Table 1). However, it is important to compare PDAE's effect on OFF-time with the effect that another exercise program, e.g., walking, has on OFF-time. Uc et al. (30) reported an effect of *d* = 0.15 on OFF-time in 49 completers with PD of 6 months of community walking, meaning that they reported slightly less OFF-time (30). Comparing the effect of PDAE to walking in the Uc study on OFF-time, *d* = 0.89, in favor of PDAE.

**Table 1 T1:** Comparison of change scores and differential effect sizes (Cohen's *d*) between 12 weeks of PDAE vs. time-matched education contact control **(A)** (EDU) and **(B)** WALK in mild–moderate PD.

		**Change scores**		***d*, PDAE**
**A. Outcome**	**Domain**	**PDAE**	**EDU**	**vs. EDU**
**Primary study outcomes**				
MDS UPDRS-IV	Motor complications	**2.23 (2.4)**	−0.3 (1.9)	1.09
Corsi product score	Spatial cognition	**6.9 (11.0)**	−3.4 (16.0)	0.76
**B. Outcome**	**Domain**	**PDAE**	**WALK^*^**	**d, PDAE vs. WALK**
OFF-time (30)	Motor complications	**2.23 (2.4)**	0.4 (1.7)	0.89

* *Data from (30); change scores >0 indicate improvement. Bold numbers indicate which group improved most*.

We explain the premise for expected improved spatial cognition and correlating measurable changes in the CNS. In our published study (56), 23 PDAE participants improved significantly on disease severity (*p* = 0.008; $\eta_{\text{p}}^{2}$ = 0.148) and spatial cognition (*p* = 0.021; $\eta_{\text{p}}^{2}$ = 0.121) compared to eight Education participants. PDAE participants also improved in executive function (*p* = 0.012; $\eta_{\text{p}}^{2}$ = 0.133). Gains were maintained 3 months postintervention. Table 1 reveals additional data from our lab comparing a contact control group (Education) vs. 18 randomly assigned participants who completed 30 h of PDAE for 3 months. Analyses of measures from the cognitive spatial domain using Corsi blocks assessment at pre- and post-20 lessons reveal a large effect between change scores of the Education group and the PDAE group (*d* = 0.76; Table 1).

This trial also examined neural mechanisms of dance-like movements for improving mobility and cognition. Before and after PDAE, participants laid in a scanner and performed a foot tapping task with the more affected limb in response to taps on their third ipsilateral metacarpal. Functional MRI (fMRI) data (atlas-based approach, *p* < 0.05) presented here are from 18 PDAE participants [7 female; age, 66.1 ± 9 years; PD duration, 6 ± 5 years; UPDRS-III, 34 ± 10; Montreal Cognitive Assessment (MoCA), 25.9 ± 3]. Posttraining, fMRI data revealed more activation in the left inferior frontal gyrus (area 45) [IFG (Figure 2A)] and the left inferior temporal gyrus (area 20) (ITG, Figure 2B). Post–pre changes in betas for each ROI correlate to improved spatial cognition in the same participants (*r* = 0.47 and *r* = 0.23). Other studies corroborate these findings: Modulation of the excitability of the IFG via rTMS was associated with enhanced cognitive processing in PD patients (60). Gray matter in the ITG increased in PD patients after balance training (61). These findings provide neural underpinnings for clinical findings, advancing understanding of pathologies and response to treatment and refining treatment approaches.

**Figure 2 F2:**
[figure not shown]
Activation patterns Post-PDAE. Increased activation was noted in left inferior frontal gyrus area 45 **(A)** and inferior temporal gyrus area 20 **(B)** at post compared to baseline after 12 weeks of PDAE.

Our central hypothesis is that PDAE is a cognitively and socially engaging, potentially neuroprotective AE, which reduces OFF-time and improves spatial cognition in PD superior to walking aerobic exercise (WALK). Our goals are to identify whether 16 months of PDAE training (partnered, complex, skilled multirhythmic, and cognitively engaging walking activities) is superior to a WALK program for reducing OFF-time, improving cognition, and slowing neurodegeneration in PD. The WALK control group controls for AE and basic walking practice to isolate the cognitive aspects required to perform skills learned in PDAE.

Here, we describe the design and rationale of a clinical trial to determine whether PDAE is more effective than WALK at addressing OFF-time in people with mild–moderate PD. The PAIRED trial will (1) investigate PDAE's relationship with OFF-time and patient-reported drug efficacy, a patient-centered outcome that has received little attention in the context of exercise studies, over short (3 months) and long terms (13 month); (2) determine whether PDAE is a robust model for simultaneously delivering cognitive, motor skill, and AE training; (3) use novel imaging techniques to evaluate rates of neurodegeneration in the SNc of PD patients after long-term exercise intervention; and (4) investigate the efficacy of a novel, long-term 13-month maintenance phase of PDAE, which may have great utility for patients if less intense maintenance periods are shown to be effective after an initial more intensive training bout. We hypothesize that PDAE will improve OFF-time superior to WALK at a 3- and 16-month follow-up, that PDAE will improve spatial cognition superior to WALK, at 3- and at 16-month follow-up, and that we will note slowed SNc NM loss and decreased iron accumulation rate in PDAE vs. WALK.

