## Study Design

### Overall Study Design

The PAIRED trial builds upon more than 10 years of research investigating unique motor, cognitive, and symptomatic benefits of PDAE. The study will perform a two arm, randomized controlled trial comparing efficacy of PDAE vs. WALK for improving OFF-time and visuospatial cognition among individuals with PD who report OFF-time. We will randomize *n* = 82 participants equally to 16 months of PDAE (*n* = 41) or to walking as aerobic exercise WALK (*n* = 41) in blocks of two to reduce variability within treatment conditions. Participants will be stratified by sex and Hoehn & Yahr (H&Y) staging (I, II, or III). The 16-month intervention period will consist of Training (3 months) and Maintenance (13 months) phases. In Training, participants will complete 20 biweekly 90-min sessions. In Maintenance, participants will complete 90-min weekly sessions. To evaluate SNc neurodegeneration over the observation period, we will image patients at study entry and 16-month follow-up using fMRI sequences. We will compare SNc volume and iron accumulation estimates in PDAE vs. WALK to assess whether PDAE is more neuroprotective.

Participants will be assessed at baseline, 3 months (immediately post-Training), and at 16 months (immediately post-Maintenance) for OFF-times, cognition, and neuroprotection, as evaluated in the SNc. At a standardized time of day, participants will be tested on all outcome measures at least 12 h after their last dose of antiparkinsonian medications. Furthermore, participants will keep an OFF-time diary to corroborate MDS-UPDRS-IV assessments. Participants will be ON medications during intervention. In addition to the primary motor and cognitive outcome measures, participants will be tested on secondary behavioral motor and cardiovascular and cognitive outcomes. Participants will undergo NM-MRI and fMRI scans at baseline and 3 and 16 months assessments to investigate mechanisms by which cognitive benefits have been obtained and replicated by PDAE and whether PDAE vs. WALK is neuroprotective, as exhibited by slowed rate of NM loss and iron accumulation and increased functional connectivity with spatial cognitive areas.

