### Analyses

#### Aim 1

We will analyze the primary study outcome with a mixed effect model (treating subject as random) with between-subjects effect of group (PDAE vs. WALK) and within-subjects timepoints (study entry, 3-month follow-up, 16-month follow-up) plus their interaction term. If the interaction term is significant, we will test differences between PDAE and WALK in the change from baseline to 3 months and from baseline to 16 months using Holm's procedure to control for multiple testing. We will consider covariates sex and H&Y staging (<III, ≥III) in the analyses.

#### Aim 2

The secondary outcome Corsi Blocks Score will be analyzed using a similar mixed effects model.

#### Aim 3

We will use similar analyses. We will use mixed effects model except that it will be a two-group (PDAE vs. WALK) and a two-level variable for time (study entry vs. 16-month follow-up).

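### The 16-month comparison tests the whole PDAE programme against WALK, so it cannot show that the 13-month Maintenance phase is itself effective

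*Protocol article*

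**What the plan says.** The last paragraph of the Introduction gives four things the trial will do. The fourth is to "investigate the efficacy of a novel, long-term 13-month maintenance phase of PDAE", which is said to be potentially useful to patients "if less intense maintenance periods are shown to be effective after an initial more intensive training bout". The Abstract says the trial will "examine effects of Training and Maintenance phases of PDAE vs. WALK on OFF-time".

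Under Overall Study Design, participants are randomised once, "equally to 16 months of PDAE (*n* = 41) or to walking as aerobic exercise WALK (*n* = 41"). The same section adds: "The 16-month intervention period will consist of Training (3 months) and Maintenance (13 months) phases". Walking Aerobic Exercise gives the WALK arm the same dose, frequency and duration as PDAE. No group has Training without Maintenance, and nobody is re-randomised at 3 months.

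Under Analyses, Aim 1, a mixed model with three timepoints is fitted. If the group-by-time interaction is significant, the trial tests "differences between PDAE and WALK in the change from baseline to 3 months and from baseline to 16 months", using Holm's procedure. The power section names the same two contrasts.

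On effects that outlast treatment, the Introduction reports that UPDRS-III scores 6 months and 1 year after a 4-week physiotherapy programme "were better than the admission scores although the therapy had been discontinued several months prior". Of the group's own earlier PDAE study it says: "Gains were maintained 3 months postintervention".

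**The concern.** The question behind the fourth purpose is whether lighter sessions after an intensive start do any good. The Introduction frames it that way itself: after the physiotherapy study, it argues that the effects would have been stronger had training gone on at lower intensity. That compares Training plus Maintenance with Training alone, and the trial observes only the first of these.

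A baseline-to-16-month difference between arms could reflect a Training effect that lasted, a Maintenance effect, or both. If it were taken as evidence for Maintenance, clinicians might adopt lower-intensity follow-on sessions on the strength of a comparison that was never made. An unseen analysis plan cannot supply the missing comparison, because no participant provides the data for it.

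**Working it through.** **1. The article's own power.** Inputs from Power and Sample Size for the Primary Outcome: d = 0.7, 41 completers per arm, alpha 0.025 and 0.05 (taken as two-sided; the text does not say). The noncentrality is 0.7 × √(41/2) = 3.17 on 80 degrees of freedom. The noncentral t gives 81.0% and 87.9%, against 81% and 88% stated. The figures reproduce.

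**2. What the 16-month contrast estimates.** Let D3 and D16 be the PDAE-minus-WALK differences in change from baseline. Write D16 = R + M. R is the difference that would remain at 16 months if both arms had stopped after Training, and M is what the two Maintenance programmes add to it. The trial observes D3 and D16. R is never observed, so M cannot be recovered. M is also itself a difference between PDAE Maintenance and WALK Maintenance, not PDAE Maintenance against none.

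**3. Illustration in points.** Table 1B gives change SDs of 2.4 (PDAE pilot) and 1.7 (cited walking study). The pooled SD is √((2.4² + 1.7²)/2) = 2.08, so d = 0.7 is 0.7 × 2.08 = 1.46 points. Suppose D3 = D16 = 1.46. Two accounts fit equally well:

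- R = 1.46, M = 0: Training lasts and Maintenance adds nothing.
- R = 0, M = 1.46: Training fades completely and Maintenance supplies everything.

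The two SDs come from separate studies, so the point value is only a scale for the example.

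**4. How often the 16-month contrast is significant when M = 0.** The method is that of step 1, with the planning effect multiplied by an assumed retained fraction. The interaction test that precedes the contrasts is left out.

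| Training effect retained | alpha 0.025 | alpha 0.05 |
|---|---|---|
| 100% | 81.0% | 87.9% |
| 75% | 53.9% | 65.1% |
| 50% | 24.8% | 34.7% |
| 25% | 7.3% | 12.3% |

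In a simulation of 10,000 runs with unit-SD changes and an assumed correlation of 0.3 to 0.7 between the 3- and 16-month changes, full retention gave significance under Holm in about 85 to 86% of runs.

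**5. What a 3-to-16-month contrast would add.** D16 − D3 = (R − D3) + M, which is the fading of the Training difference plus M. In the same simulation with full retention and M = 0 it rejected in 5.2 to 5.5% of runs, close to its nominal 5%. So it is not driven by an effect that merely persists. It is zero under both accounts in step 3, so it does not identify Maintenance efficacy either.

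Its precision, in SD units with 41 per arm, is a 95% half-width of 1.99 × √(2/41) × √(2(1 − ρ)). That gives 0.52, 0.44 and 0.34 for ρ = 0.3, 0.5 and 0.7. It is informative beside d = 0.7, but not sharp.

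**The case against.** The strongest reply is that the fourth purpose is one clause in an introduction. Overall Study Design sets three formal aims (OFF-time, spatial cognition, neurodegeneration), and Maintenance efficacy is not one of them. The stated hypotheses concern PDAE against WALK at 3 and 16 months, and the planned contrasts answer them. The Abstract's wording is comparative and can be read as superiority at the end of each phase, with WALK as concurrent control. All of this stands, and it confines the point to the claim about Maintenance.

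A reader might infer more than the documents support:

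- *That the 16-month comparison is invalid.* It is not. It is a randomised comparison of two whole programmes.
- *That the trial sets out to show Maintenance works, or plans to report the result that way.* The verb is to investigate, and the statement on usefulness is conditional. No passage says how a positive result will be reported.
- *That carry-over is established for the primary outcome.* The physiotherapy follow-up concerns UPDRS-III. For UPDRS-IV the article reports only the improvement after 4 weeks. The PDAE finding follows results on disease severity, spatial cognition and executive function, and covers 3 months, not 13.
- *That the Maintenance share lies between 0% and 100%.* It is simply not identified. R could exceed D16 or fall below zero.
- *That leaving out a 3-to-16-month contrast is an error.* A secondary contrast may sit in the analysis plan, which is not shown.

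None of this answers the central difficulty. The same sentence that says investigate also speaks of Maintenance being shown to be effective, and the design has no comparison that could show it.

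**Conclusion.** The point holds for the claim about Maintenance and for nothing wider. The trial can say whether 16 months of PDAE, Training followed by Maintenance, beats 16 months of WALK. It cannot say whether Maintenance contributed.

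The non-identification follows from the design and needs no assumption. Its practical size does need some. With the planning effect of 0.7 and no Maintenance effect at all, the 16-month contrast would be significant 81% or 88% of the time under full retention and 25% or 35% under half retention. The retained fractions, the two-sided alpha and the correlation between changes are assumptions, and the documents do not give them. The change is worth making because it alters what can be concluded about one stated purpose at almost no cost.

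**What to change.** 1. Reword the fourth purpose in the Introduction, and the matching line in the Abstract, to ask whether the PDAE-WALK difference seen after Training is still present at 16 months under the full programme of Training followed by Maintenance.
2. Report the between-arm contrast in change from 3 to 16 months, with its confidence interval, from the mixed model already planned. Label it a secondary estimate of persistence, not of Maintenance against no Maintenance. If the analysis plan already has it, refer to it there.
3. State that no efficacy claim will be made for Maintenance as such, because no group receives Training without it.

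The cost is some wording and one extra estimate. There are no new participants, visits or data, and the primary hypotheses, Holm levels and power stay as they are. The downside is a narrower claim about Maintenance.
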